## 2. General Principles of Analysis

- 1) All statistical analyses of the clinical trial results will be based on two-sided testing, with a significance level of 5%.
- 2) The statistical software used for analysis will be SAS® Version 9.4 (SAS Institute Inc., Cary, NC).
- 3) For continuous data, the mean and 95% Confidence Interval will be presented. For categorical data, frequency and percentage (%) will be presented.
- 4) If necessary, a subgroup analysis will be performed by categorizing subjects based on their initial characteristics from the screening or baseline visits.

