## 2. Secondary Outcome Measures

- 1) The changes in the following secondary outcome measures from baseline to Day 7 will be tested using the same method as the primary efficacy endpoint: Nasal Congestion Severity Score, Nasal Symptom Score VAS, Systemic Symptom Score VAS, WURSS-21-K symptom score, WURSS-21-K quality of life score, and EQ-5D-5L score. Additionally, the pre- and post-treatment differences within each group will be analyzed using a Student's paired t-test, depending on the normality of the data.
- 2) To compare the differences in trends between the groups, Repeated Measures Analysis of Variance (RM ANOVA) will be used, with Dunnett's procedure for multiple comparisons (comparing each time point against baseline).
- 3) The Global Evaluation of Efficacy satisfaction and cold recovery status at Day 7 will be analyzed using the Chi-square test. However, if the Global Evaluation of Efficacy satisfaction score is treated as a continuous variable, an Independent t-test or Wilcoxon rank-sum test will be performed.

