#### 2) Rationale

This clinical trial is designed to evaluate the efficacy and safety of GGTCS for patients with nasal congestion due to the common cold. The primary outcome measure is the WRUSS-21-K. The change in the WRUSS-21-K from baseline to Day 7 (after a total of 21 doses, 3 times a day for 7 days) will be compared between the test group (GGTCS) and the control group (placebo).

The hypothesis for this clinical trial is as follows:

[Hypothesis]  $H_0$ (Null Hypothesis):  $\mu_t = \mu_c$  vs.  $H_1$ (Alternative Hypothesis):  $\mu_t \neq \mu_c$

$\mu_t$  : The mean change in the WRUSS-21-K score from baseline to Day 7 in the test group.

$\mu_c$  : The mean change in the WRUSS-21-K score from baseline to Day 7 in the control group.

Table 1. Change in WRUSS-21-K of Eungyo-san, Sams0-eum, placebo between pre- and post-treatment.

|                   | Pre-Treatment | Post-Treatment | Change (Before-After)* |
|-------------------|---------------|----------------|------------------------|
| Eungyo-san (n=44) | 56.28(30.47)  | 13.86(22.43)   | 44.00(22.27)           |
| Sams0-eum (n=42)  | 54.74(30.98)  | 17.05(24.29)   | 40.12(18.78)           |
| Placebo (n=42)    | 66.48(31.64)  | 33.33(30.02)   | 29.09(21.89)           |

\*: Change adjusting WRUSS-21-K score of baseline.

Previous studies (K.-I. Kim, M. Hong) showed that the mean (standard deviation) change in the WRUSS-21-K score from pre- to post-treatment was 29.09 (21.89) for the placebo group, 44.00 (22.27) for the Eungyo-san treatment group, and 40.12 (18.78) for the Samso-eum treatment group. The mean difference in effect was 14.91 for the Eungyo-san treatment group compared with the placebo group, with a pooled standard deviation of 22.09. The mean difference in effect for Samso-eum compared with the placebo group was 11.03, with a pooled standard deviation of 20.39. In this clinical trial, the significance level ( $\alpha$ ) was set at a two-sided 5%, and the power ( $1-\beta$ ) is 80%. Based on the results of the previous studies, the effect difference is set at 10 and the standard deviation at 21. The calculated number of subjects required to confirm the effect of the GGTCS group compared with the placebo group is as follows.

$$\left\{ \frac{2 \left( z_{1-\frac{\alpha}{2}} + z_{\beta} \right)^2 * \sigma^2}{|\mu_T - \mu_c|} \right\} = \left\{ \frac{2(1.96 + 0.84)^2 * 21^2}{10^2} \right\} = 69.227 \approx 70$$

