**10.3.2.8.Global Evaluation of Efficacy**

- This is a 0-4 point scale to assess the overall satisfaction with the treatment. The subject will self-evaluate (0=very good, 1=good, 2=average, 3=poor, 4=very poor).
- This will be assessed at Visit 3.

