### **11.1.4. Analysis of Demographic and Baseline Data**

Descriptive statistics for demographic and pre-treatment subject characteristics will be presented by group. Continuous variables will be analyzed using an independent t-test or Wilcoxon rank sum test depending on normality. Categorical variables will be analyzed using a Chi-square test or Fisher's exact test.

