### **11.2.2. Secondary Outcome Measures**

- 1) The change from baseline to Day 7 in Nasal Congestion Severity Score, Nasal Symptom Score VAS, Systemic Symptom Score VAS, WURSS-21-K symptom and quality of life scores, EQ-5D-5L score, and duration of cold symptoms will be tested using the same method as the primary outcome measures.
- 2) To compare the differences in trend changes between groups, a Repeated Measures Analysis of Variance (RM ANOVA) will be used, with Dunnett's procedure for multiple comparison correction (comparing each time point to baseline).
- 3) The Global Evaluation of Efficacy satisfaction and cold recovery status on Day 7 will be analyzed using a Chi-square test. If the Global Evaluation of Efficacy score is treated as a continuous variable, an Independent t-test or Wilcoxon rank sum test will be performed.

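### The five-level Global Evaluation of Efficacy is assigned a Chi-square test that ignores the order of the ratings, with an undefined option to use a t-test or Wilcoxon test instead

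*Protocol*

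**What the plan says.** Protocol section 10.3.2.8 defines the rating, taken at Visit 3, as "0=very good, 1=good, 2=average, 3=poor, 4=very poor". These are five levels with a clear order, lower being better.

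Section 11.2.2, item 3, sets the analysis: "The Global Evaluation of Efficacy satisfaction and cold recovery status on Day 7 will be analyzed using a Chi-square test". One test is thus named both for this five-level rating and for recovery status, which section 10.3.2.7 describes as a yes/no outcome. The next sentence adds: "If the Global Evaluation of Efficacy score is treated as a continuous variable, an Independent t-test or Wilcoxon rank sum test will be performed". The synopsis says the same: "if the Global Evaluation of Efficacy satisfaction score is treated as a continuous variable, an Independent t-test or Wilcoxon rank-sum test will be performed".

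Neither place says what would cause the score to be handled as continuous, or which of the two further tests would then apply. For baseline variables section 11.1.4 does give a rule: "Continuous variables will be analyzed using an independent t-test or Wilcoxon rank sum test depending on normality". All tests are two-sided at 5% (section 11.1.2 and synopsis).

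**The concern.** There are two separate weaknesses.

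- **The default test ignores order.** A Pearson Chi-square test on a 2 × 5 table gives the same result however the five columns are arranged. The question of interest is whether ratings move towards the good end under GGTCS. A test with 4 degrees of freedom spreads its sensitivity over patterns nobody is looking for, so it detects a one-directional shift less often than a test that uses the order.
- **Three tests are available for one outcome.** The protocol names a default and two alternatives but no trigger. Taken alone, the text would let the choice be made after the ratings are known, and the 5% level would then not be protected.

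The stake is the credibility and sensitivity of one secondary outcome. The primary analysis and the sample size do not depend on it.

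**Working it through.** **Inputs from the protocol.** Five ordered levels (10.3.2.8); two-sided 5% (11.1.2); 70 per group evaluable and 88 per group randomised (5.3).

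**The protocol's own figure.** With difference 10, SD 21 and 80% power, n = 2(1.960 + 0.842)² × 21² / 10² = 69.2, rounded up to 70 per group; 70 / 0.8 = 87.5, rounded up to 88. This reproduces, but it concerns WURSS-21-K only. No power, distribution or effect is stated for the Global Evaluation, so everything below rests on assumptions.

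**Step 1: loss from the extra degrees of freedom.** For a 1-df test with power P, the noncentrality is λ = (1.960 + z_P)². Giving the same λ to a 4-df Chi-square test:

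| Power, 1 df | λ | Power, 4 df | Loss (points) |
|---|---|---|---|
| 50% | 3.84 | 31% | 19 |
| 60% | 4.90 | 39% | 21 |
| 70% | 6.17 | 48% | 22 |
| 80% | 7.85 | 60% | 20 |
| 90% | 10.51 | 74% | 16 |

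**Step 2: one case by hand.** Assume control ratings of 10/20/40/20/10% and an odds ratio of 2. Each cumulative proportion c becomes 2c/(1 + c), so 0.10, 0.30, 0.70, 0.90 become 0.182, 0.462, 0.824, 0.947. The treated ratings are then 18.2/28.0/36.2/12.4/5.3%. With 88 per group, λ = 88 × Σ(p − q)²/(p + q) = 88 × 0.0715 = 6.29. That gives 49% power on 4 df. A 1-df test with the same λ has power Φ(√6.29 − 1.96) = Φ(0.55) = 71%.

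**Step 3: simulation.** 20,000 trials per setting; several assumed control distributions (symmetric, flat, and skewed towards good ratings); proportional-odds shift; Pearson Chi-square on all five levels against tie-corrected Wilcoxon. Loss of power for the Chi-square, in points, across the distributions:

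| Odds ratio | 70 per group | 88 per group |
|---|---|---|
| 1.5 | 11–12 | 13–14 |
| 2.0 | 22–23 | 22–23 |
| 2.2 | 22–23 | 20–22 |
| 2.5 | 19–21 | 14–17 |
| 3.0 | 12–14 | 7–8 |

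The Monte Carlo standard error of each power is at most √(0.25/20,000) = 0.35 points. Allowing for that, the range is roughly 7 to 24 points. For the Step 2 distribution with 88 per group, Chi-square against Wilcoxon is 18% against 31% at odds ratio 1.5, 49% against 71% at 2.0, and 91% against 98% at 3.0.

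**Step 4: a case with no loss.** In one simulated non-monotone difference, the Chi-square test had 96% power and the Wilcoxon test 6%.

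**Step 5: choosing among the three tests.** With no treatment difference, each test alone rejects in about 5% of trials (Chi-square about 4.3–5.2%). If the smallest of the three p-values is always reported, rejection rises to about 8.5–9.5%.

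**The case against.** Four points can fairly be made for the protocol.

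- **A figure of about 20 points lost would be too strong as a general statement.** A reader might infer it from the cases near an odds ratio of 2. The documents give no distribution or effect for this rating, and the loss falls to 7–8 points at an odds ratio of 3 with 88 per group. This stands: only the range, with its assumption, can be claimed.
- **The two harms do not add together.** Power is lost only if the Chi-square test is reported; type I error rises only if another test is picked because its result is better. The Wilcoxon test is also already permitted, so the loss is possible rather than built in. This stands too.
- **The documents do not say that the choice will follow the data.** A SAP, not available here, could settle it before unblinding, and section 6.3 keeps the allocation list closed until the study is completed. Nor does the protocol say that the Chi-square test uses all five levels ungrouped, though that is the natural reading. These points limit the concern. They do not remove it, because the protocol itself names the default test and writes in the open option.
- **Small expected counts do no demonstrated harm.** A reader might infer that rare extreme ratings invalidate the Chi-square test. Expected counts below 5 are common when a level holds only 3–5% of controls, but the simulated type I error stayed close to 5%.

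**Conclusion.** The point holds in a limited form. An ordered five-level outcome is assigned a test that ignores order, together with an option that has no trigger.

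If the Chi-square test is applied to all five levels, it gives up roughly 7 to 24 points of power against a Wilcoxon test. This assumes a proportional-odds shift with odds ratio 1.5 to 3 and 70 to 88 per group; a non-monotone difference would reverse the comparison. If instead the best of the three tests were reported, type I error would be about 8.5–9.5% against a nominal 5%. That is a worst case, not something the protocol says will happen.

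The consequence is small, since one of ten secondary outcomes is involved. The Chi-square test remains suitable for recovery status.

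**What to change.** In section 11.2.2, item 3, and in the matching item of the synopsis:

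- name the Wilcoxon rank-sum test as the only between-group test for the Global Evaluation of Efficacy;
- if an effect estimate is wanted, add a proportional-odds odds ratio with its 95% confidence interval, as an estimate and not as a second test;
- delete the sentence that lets the score be handled as continuous;
- keep the Chi-square test for the binary recovery status.

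The cost is one sentence changed in two places. Data collection, sample size and trial conduct are unaffected.

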### **11.2.3. Exploratory Outcome Measures**

The analysis of pattern identification will follow the analysis methods for the efficacy outcome measures.

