## 3. Exploratory Outcome Measures

- The analysis methods for comparing different syndromes will be the same as those for the efficacy outcome measures.

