Based on the 1:1 allocation ratio between the treatment and control groups, the required number of subjects per group is 70. Considering a 20% dropout rate for this clinical trial, a total of 176 subjects (88 per group) are needed.

Subjects will be recruited from multiple centers, with a target of 88 subjects from Daejeon University Daejeon Korean Medicine Hospital, and 44 subjects each from Kyung Hee University Korean Medicine Hospital and Pusan National University Korean Medicine Hospital. However, the number of subjects recruited per center may vary depending on the recruitment speed. The final allocation of subjects per center will be re-evaluated by the Central Data Management (DM) team at the midpoint (50%) of the total study period, based on the recruitment speed of each center. If the number of subjects per center changes, an independent statistician will generate new codes as needed, considering the block size, and these will be reflected in the randomization schedule for each center. Investigational products will be provided to each study site based on their initial number of subjects. Additional products for sites with increased subject numbers will be provided by the drug manufacturer (National Institute of the Korean Medicine Development) according to the newly generated randomization codes. Sites with a reduced subject number will be instructed to discard the remaining randomization codes.

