#### 11) Pattern Identification for Common Cold Questionnaire

- It will be used to classify the subject's pattern type to see if there is an effect difference by pattern.
- It classifies the patterns as Wind-Cold type, Wind-Heat type, or other types.
- It will be assessed at Visit 1.

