**10.5. Exploratory outcome measures****10.5.1. Questionnaire for Common Cold Pattern Identification**

- To examine the difference in effects by pattern identification, it will be used to classify subjects' patterns.
- It classifies pattern types into 8 categories: Wind-Cold type, Wind-Heat type, Dampness type, Summer-Heat type, Qi deficiency type, Blood deficiency type, Yin deficiency type, and Yang deficiency type. In this study, the six pattern types other than Wind-Cold and Wind-Heat types will be classified as 'Other' to create a total of three pattern types (Wind-Cold type, Wind-Heat type, and Others).
- This will be assessed at Visit 1.

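### The exploratory pattern outcome asks whether the GGTCS effect differs by pattern, but the methods assigned to it contain no comparison of the effect across patterns

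*Protocol*

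**What the plan says.** The question is stated twice. Protocol 10.2.1, item 11, says of the pattern questionnaire: "It will be used to classify the subject's pattern type to see if there is an effect difference by pattern". Section 10.5.1 gives the same purpose, "To examine the difference in effects by pattern identification", and reduces eight pattern types to three: Wind-Cold, Wind-Heat and Others. The synopsis lists the change in WURSS-21-K total score by pattern as the only exploratory outcome.

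The analysis is also stated twice, each time by cross-reference. Section 11.2.3: "The analysis of pattern identification will follow the analysis methods for the efficacy outcome measures". Synopsis, Statistical Analysis: "The analysis methods for comparing different syndromes will be the same as those for the efficacy outcome measures".

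The methods referred to are in 11.2.1 and 11.2.2:
- ANCOVA with group as the effect and baseline WURSS-21-K total as covariate, with further covariates if necessary;
- repeated-measures ANOVA for trends over time;
- chi-square, t or Wilcoxon tests for the global evaluation, and chi-square for recovery.

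Section 11.1.2, item 4, allows subgroup analysis by categorising patients on baseline characteristics. Section 6.3 states that randomization is not stratified.

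**The concern.** Whether an effect differs by pattern is a question about a difference between treatment effects. It needs a model or contrast that sets the GGTCS-placebo difference in one pattern against that in another. None of the cross-referenced methods does so.

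Followed as written, the text leads most naturally to a separate GGTCS-placebo ANCOVA in each pattern. That gives three tests of whether there is an effect, and none of whether the effects differ. Each test uses only a fraction of a sample sized for one overall comparison. A pattern can therefore be significant or not because of its size or by chance, even when the drug works equally well in all three. A reader who sets a significant pattern beside a non-significant one would be reading noise as effect modification.

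**Working it through.** **Inputs.** From 5.3 of the protocol: "the effect difference is set at 10 and the standard deviation at 21", two-sided 5% significance, 80% power; "Based on the 1:1 allocation ratio between the treatment and control groups, the required number of subjects per group is 70"; 88 per group after 20% dropout. Section 5.3 also supplies a larger effect for sensitivity: "The mean difference in effect was 14.91 for the Eungyo-san treatment group compared with the placebo group". Section 10.5.1 gives three patterns. The pattern shares are **not in the protocol**, so they are assumed and varied from equal thirds to 90/5/5. SD 21 is taken as the residual SD in every pattern.

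**Step 1: the plan's own figure.** n = 2(z₀.₉₇₅ + z₀.₈₀)² σ²/δ² = 2 × (1.960 + 0.842)² × 21²/10² = 69.23, so 70 per group. 70/0.8 = 87.5, so 88. Both reproduce. Overall power (normal approximation) is 80.4% at 70 per group and 88.5% at 88.

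**Step 2: do the stated methods compare effects across patterns?**

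| Provision | What it gives | Compares effect by pattern? |
|---|---|---|
| 11.2.1 ANCOVA, group + baseline | one GGTCS-placebo difference | No |
| 11.2.1 optional covariates | pattern as a main effect at most | No |
| 11.2.2 repeated-measures ANOVA | group trends over time | No |
| 11.2.2 chi-square, t, Wilcoxon | two-arm comparison | No |
| 11.1.2 subgroup clause | categories of patients | No test named |

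**Step 3: separate tests when the effect is the same in every pattern.** With n per arm in a pattern, SE = 21√(2/n), and power p comes from the two-sample noncentral t. A mixed picture means at least one pattern significant and at least one not:

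P(mixed) = 1 − p₁p₂p₃ − (1−p₁)(1−p₂)(1−p₃).

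Equal thirds of 70: n = 23.3, SE = 21√(2/23.3) = 6.15, δ/SE = 1.63, p = 0.356. P(mixed) = 1 − 0.356³ − 0.644³ = 1 − 0.045 − 0.267 = 0.69.

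Shares 50/30/20 of 70: n = 35, 21, 14; p = 0.50, 0.33, 0.23. P(mixed) = 1 − 0.037 − 0.259 = 0.70.

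| Assumed shares | P(mixed), effect 10, 70 per arm | P(mixed), effect 10, 88 per arm |
|---|---|---|
| equal thirds | 69% | 74% |
| 50/30/20 | 70% | 76% |
| 60/30/10 | 73% | 79% |
| 80/10/10 | 76% | 84% |
| 90/5/5 | 79% | 87% |

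**Step 4: other common effects,** over the same shares and both sample sizes:
- effect 14.91: 54 to 97%;
- effect 5: about 32 to 38%, counting significance in favour of GGTCS (counting both tails adds at most about two points);
- no effect: 1 − 0.95³ − 0.05³ = 14%.

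**Step 5: the alternative.** One ANCOVA with group, pattern, group-by-pattern and baseline, with a 2-df F test of the interaction, was simulated (1,500 runs per scenario).
- With the same effect in every pattern (10 or 0), it declares a difference in about 4 to 6% of trials.
- With true effects of 15, 5 and 10 in the three patterns, its power is about 8 to 22%.
- With true effects of 20, 0 and 10, its power is about 17 to 70%.

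Separate ANCOVAs in the same simulation gave 69% (70 per arm) and 74% (88 per arm) mixed results for equal thirds at effect 10, agreeing with Step 3.

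**The case against.** The strongest reply is that 11.2.3 is a one-sentence pointer for a single exploratory outcome. It names a family of methods and does not exclude an interaction term, and model terms of this kind are often left to a statistical analysis plan, which is not shown here. This stands in part: nothing in the protocol forbids an interaction. But the protocol does more than stay silent. It assigns methods, in two places, and those methods do not answer the question it poses in two other places. An analysis plan that followed the text would inherit the mismatch.

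Three stronger readings should be resisted.

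- **That the analysis will usually suggest a difference that does not exist.** This would require separate tests, readers who contrast their p-values, and a true effect near 10 or larger. At an effect of 5 or nil, mixed results are the minority. A mixed picture is also not a declared difference. The protocol does not say one will be inferred, and 11.2.1 already calls for the difference with its 95% confidence interval.
- **That the patterns will be compared with the arms pooled.** The synopsis wording could be taken that way, but 10.2.1 and 10.5.1 both speak of the effect by pattern, so this reading is strained.
- **That a trial objective is compromised.** Section 4 states the objective as efficacy and safety against placebo, without mention of pattern. Comparison by Korean medicine diagnosis appears in 6.2 in a list under the trial procedure, and pattern is classed as exploratory.

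It is also fair to say that the interaction test gains little power. Its benefit is a controlled false-difference rate and a clear reading of the result.

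**Conclusion.** The point holds as a mismatch between an exploratory question and the method assigned to it: no analysis named in the protocol compares the GGTCS effect across the three patterns. If the text is carried out as a separate ANCOVA in each pattern, and the planned effect of 10 is the same in all of them, a mixed significant and non-significant picture arises in roughly 70 to 80% of trials at 70 per arm, against about 5% in which an interaction test would declare a difference. The percentage depends strongly on the true effect and only moderately on the assumed shares; the absence of a between-pattern comparison depends on neither. Nothing here touches the primary analysis. The change is worth making because it is cheap and the question is one the protocol itself asks.

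**What to change.** In 11.2.3 and in the exploratory paragraph of the synopsis, replace the cross-reference with text to this effect: the Day 7 change in WURSS-21-K total score is analysed by the primary ANCOVA with pattern (Wind-Cold, Wind-Heat, Other) and the group-by-pattern interaction added; the interaction test and the GGTCS-placebo difference with its 95% confidence interval in each pattern are presented; a difference in effect by pattern is not inferred from separate p-values. Add that the analysis is exploratory and that power for the interaction is low.

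The cost is a few sentences and the added pattern and interaction terms, on data already collected at Visit 1. It should be settled before unblinding. The downside is that a non-significant interaction will say little, and a pattern with very few patients will have a wide interval, so the within-pattern estimates remain descriptive.
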